### Randomization

Therapists will be randomly assigned either to a training group in which they will undergo an intensive training of the short-term STPP manual for social phobia as developed for the multi-centre study or to a control group in which the non-manualized standard psychodynamic treatment is applied. Randomization will be stratified taking into account the three trial sites. Randomization of therapists will be performed centrally by IZKS Mainz before training of the therapists starts. Patients will not be randomized and will not know whether their therapist was recently trained in STPP for SP or not.

### Statistical analysis

#### Primary analysis

The following hypothesis will be tested:

H_0_: π_manualized _≤ π_standard _vs. H_1_: π_manualized _> π_standard_

where π_manualized _and π_standard usual _are the true remission probabilities in the manualized treatment group and the standard routine care group after treatment period respectively.

Remission rates will be compared between specifically trained STPP (manualized) and psychodynamic treatment as usual (standard) group by logistic regression with covariates for treatment, sex of the therapist, and experience of the therapist. Due to the cluster randomized nature of the study a term for the therapist will be added. Within each therapist compound symmetry will be assumed. Intent-to-treat analyses (LOCF) as well as completer analyses will be conducted. Drop-outs will be considered as non-responders/non-remitters in the analysis. As sensitivity analyses a chi-square test and a conditional logistic regression adjusted for the therapist will be performed. Also the LSAS will be analysed as a continuous measure by means of mixed model with repeated measurements for the ITT population. Replacement strategies of missing values will be discussed after assessing the pattern of the missing value structure.

#### Secondary analyses

Self-report questionnaires and observer ratings (SPAI, CGI, BDI, FSKN, DKB-35, CDS, BSSS, EQ-5D, HAQ, treatment adherence) will be analysed by mixed models with repeated measurements. Further analyses will include

• cross-sectional analyses comparing therapists;

• subgroup analyses of subjects' and therapists' conditions

• costs of the SP treatment (CSSRI)

All analyses will be conducted on a one-sided level of significance of 0.05. Descriptive statistics showing the measurements over time will be presented whenever appropriate.

Serious adverse events and drop-outs will be analysed descriptively.

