### Sample size calculation

Being aware of the controversy whether RCT and efficacy studies reach the same effect sizes we used two recent meta-analyses on RCTs in STPP to estimate expected effect sizes. Abbass et al. (2006) [22] included trials on STPP with the majority of them (8 out of 13) not reporting manualized treatments. This condition comes closest to our comparison group receiving standard psychodynamic treatment. For general psychiatric symptoms effect sizes were medium (short term outcome d = .42, long term outcome d = .51). Based on the fact that effect sizes for specific target problems are usually larger, both treatment conditions will be expected to be superior to treatment as usual or no treatment. Both treatments seem to be highly acceptable and detrimental effects are not expected.

In their meta-analysis, Leichsenring et al. (2004) [23] reported effect sizes (prae-post) of d = .90 for the reduction of general psychiatric symptoms by STPP based on strictly manualized treatments. Compared to the results of Abbass et al. (2006) [22] with mostly non-manualized STPP we expect the between group effect size to be medium (about d = .48). Therefore, we pragmatically expected an effect size of 0.50 between the two groups (trained versus non trained therapist). In order to detect this difference at alpha = .05 (one-tailed) with a power of 0.80, N = 42 (one-tailed) patients per group are required according to the formula of Campbell et al. (2001) [24] for Cluster-Randomization, given that an average of 2 patients per therapist will be treated:

(z_α _= z-value for probability of error type I alpha, z_β _= z-value for probability of error type II beta, σ = standard deviation of outcome, E = expected ES of outcome, m = mean observations for each cluster, ρ = Intracluster correlation coefficient (ICC), ES = E/σ = standardized effect size)

While planning this study no meaningful published data on remission rates for manualized vs. non-manualized psychodynamic psychotherapy of social anxiety disorders were available. We based sample size calculation on available meta-analyses on psychodynamic psychotherapy all based on continuous outcomes. Estimating the sample size needed for a dichotomous approach (remission rates), we introduced the following conservative assumptions:

a) The ICC was set to 15%, which is high for comparable studies. According to Campbell (2001) [24] the ICC for outcome variables could be assumed to be less than 5%.

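### The one-sided 0.05 level covers every analysis, including therapist and subgroup comparisons for which the plan states no direction

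*Protocol article*

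**What the plan says.** The level is set in one sentence near the end of Secondary analyses: "All analyses will be conducted on a one-sided level of significance of 0.05". It follows a list of further analyses that includes "cross-sectional analyses comparing therapists" and "subgroup analyses of subjects' and therapists' conditions", and nothing exempts either item.

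The article states a direction in three places:

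- Objectives and hypotheses, first hypothesis: treatment effects are better with trained than with untrained practitioners.
- Objectives and hypotheses, second hypothesis: treatment duration and costs fall.
- Primary analysis: the alternative hypothesis is a higher remission probability under manualized treatment.

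The sample size section uses the same level for the main comparison: "In order to detect this difference at alpha = .05 (one-tailed) with a power of 0.80". Serious adverse events and drop-outs are to be described, not tested.

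**The concern.** A one-sided test needs a direction chosen before the data are seen. For differences among therapists or between subgroups the plan gives none, and for some of these comparisons none can exist. The analyst must then either choose a direction after seeing the results, which doubles the nominal error rate, or decide privately what one-sided 0.05 means for a test without direction. It could be read as a 5% test or, through its two-sided equivalent, as a 10% test.

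The harm direction also matters. If the secondary treatment effects are reported only through one-sided superiority tests, a worse result under training cannot reach formal significance, however large it is.

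**Working it through.** **1. Which analyses have a direction**

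| Analysis | Direction stated? | One-sided 0.05 defined? |
|---|---|---|
| Primary remission test and its sensitivity analyses | Yes, Primary analysis | Yes |
| Treatment effects on secondary scales | Yes, first hypothesis | Yes |
| Duration and costs | Yes, second hypothesis | Yes |
| Comparisons among therapists | No | Not for an omnibus test |
| Subgroup contrasts | No | Only if a direction is added |
| Comparison of efficacy and effectiveness designs, and of fields of care (further objectives) | No | Only if a direction is added |

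**2. Therapist comparison.** The planning figures are 42 completers per group and a mean of 2 patients per therapist ("N = 42 (one-tailed) patients per group are required"; "given that an average of 2 patients per therapist will be treated"). That gives 42 / 2 = 21 therapists per group. A joint test over 21 therapists has 20 degrees of freedom. Its F or chi-square statistic rejects only in the upper tail, but it responds to differences in any direction. No one-sided version exists.

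**3. Subgroup contrast with one degree of freedom.** Let Z be standard normal under the null hypothesis; the one-sided critical value is 1.645.

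- Direction fixed beforehand: P(Z > 1.645) = 0.05.
- Direction taken from the observed sign: P(|Z| > 1.645) = 2 × 0.05 = 0.10.
- Two-sided 5% test: P(|Z| > 1.960) = 0.05.

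**4. Visibility of a worse result on a secondary scale.** Illustration with the plan's own inputs: 42 per group, ICC 0.15, cluster size 2, and the planned effect ("we pragmatically expected an effect size of 0.50 between the two groups") with its sign reversed, d = −0.50. Applying these to a secondary scale is an assumption.

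- Design effect = 1 + (2 − 1) × 0.15 = 1.15.
- Effective n per group = 42 / 1.15 = 36.5.
- Standard error = √(2 / 36.5) = 0.234, so d / SE = −2.137.
- One-sided superiority test rejects: P(Z > 1.645 + 2.137) = 0.00008, and any such rejection would be in favour of training.
- Two-sided 95% interval lies wholly on the adverse side: P(Z < −1.960 + 2.137) = 0.57.

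**5. Sample size.** It rests on the primary comparison alone, so a change of level for undirected analyses leaves it as it is. With the stated inputs, the usual formula 2 × ((1.645 + 0.842) / 0.50)² × 1.15 gives 56.9, or 57 per group, and does not reproduce the stated 42. That is a separate matter, and nothing in this point depends on it.

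**The case against.** The best defence is that the trial's question is directional throughout, that harm is not anticipated, and that the details of exploratory tests belong in an analysis plan that is not shown. Much of this stands, and it rules out several stronger readings.

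- A reader might infer that the chi-square sensitivity analysis has no one-sided form ("As sensitivity analyses a chi-square test"). It compares remission between two groups, so it has one degree of freedom. Its signed root is a two-proportion z-test, and Primary analysis fixes the direction.
- A reader might infer that the mixed models rely on an omnibus group-by-time test. The article names no such test, and these models allow a directional contrast at one visit.
- A reader might infer that the error rate is doubled on all ten secondary measures and compound this over ten tests. The first hypothesis gives treatment effects a direction, so their one-sided error rate is 5%. The number of therapist and subgroup tests is not given, so no overall figure can be derived for them either.
- A reader might object to one-sided cost tests. The second hypothesis states their direction.
- A reader might conclude that the trial cannot show harm. That is true only of formal testing on the efficacy scales. Descriptive statistics over time, descriptive analysis of serious adverse events and drop-outs, and the recording of new psychiatric diagnoses could all show an adverse trend.

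Some of the subgroup work is also defensible as written. A treatment effect within a subgroup can borrow the direction of the first hypothesis, and a therapist comparison that meant only trained against untrained could do the same. The article does not say that this is what it means. The appeal to an unseen analysis plan does not remove the point, because the article itself fixes the rule and makes it universal.

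**Conclusion.** The point holds in a narrow form and is minor. The rule as stated is undefined for an omnibus comparison of more than two therapists, and it has no fixed direction for contrasts between subgroups. The size is a false positive rate of 10% instead of 5% for each one-degree-of-freedom contrast, on the assumption that the direction is picked after seeing the data. The article does not say that this will happen; it only leaves it open. The primary test, its sensitivity analyses, treatment effects under the first hypothesis, and duration and costs are properly one-sided as the plan stands. Two-sided intervals for secondary treatment effects are advisable so that a worse result is visible, but their absence does not mean that harm would go unseen.

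**What to change.** Replace the blanket sentence with a rule in three parts:

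1. One-sided 0.05 applies to analyses with a stated direction: the primary remission test and its sensitivity analyses, treatment effects under the first hypothesis, and duration and costs under the second. Say which secondary measures count as treatment effects; helping alliance and social support are not obvious cases.
2. Comparisons among therapists, subgroup comparisons and other undirected comparisons are tested two-sided at 5%. Omnibus tests are simply run at 5%.
3. Two-sided 95% confidence intervals are reported for all secondary treatment effects.

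This costs a few lines of text and changes neither the primary test nor the sample size. The threshold for an undirected contrast rises from 1.645 to 1.960, so some exploratory results will look weaker. A directed result with a one-sided p-value between 0.025 and 0.05 will come with a 95% interval that includes no effect, and the report should explain this.

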### Safety aspects

Safety parameters will comprise newly occurring psychiatric diagnoses (SCID-I) and all serious adverse events that are reported during and up to six months after treatment.

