### Interventions

The manualized treatment approach is based on Luborsky's Supportive Expressive Therapy (SET). The treatment includes the characteristic elements of SET therapy, that is, setting goals, focus on the Core Conflictual Relationship Theme (CCRT) associated with the patient's symptoms, interpretive interventions to enhance insight into the CCRT, and supportive interventions, in particular fostering a helping alliance. In order to tailor the treatment more specifically to social phobia, treatment elements have been added, for example informing the patient about the disorder and the treatment, a specific focus on shame and on unrealistic demands, and encouraging the patient to confront anxiety-provoking situations. More directive interventions are included as well, such as specific prescriptions to stop persisting self-devaluations [10]. The treatment is designed for a time limited approach with 25 individual sessions of STPP over 6 months (as reimbursed by German health insurance).

Those patients who are treated in the control condition will receive standard psychodynamic treatment.

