### Assessment

The time points of assessment are shown in Figure 1. Assessments will be conducted before treatment starts, after 8 and 15 weeks, after 25 treatment sessions, at the end of treatment, 6 months and 12 months after termination of treatment. If treatment exceeds 25 sessions additional post-treatment assessment is performed immediately after termination.

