### Objectives and hypotheses

The research questions of this trial are:

(1) How can manualized STPP be implemented into routine outpatient care?

(2) Will the new methods lead to an improvement of treatment courses and outcomes?

(3) Will treatment effects reached in routine psychotherapeutic treatments be comparable to those of the controlled, strictly manualized treatment of the main study?

The major hypotheses are: (1) Treatment effects reached by private practitioners trained with the manualized procedure of STPP of the main trial will be superior to therapists who apply their usual psychodynamic treatment. (2) Implementation of manualized STPP will lead to an average reduction of treatment duration and costs.

Further objectives: a) direct comparison (using the same measures) of results based on an efficacy and an effectiveness design; b) comparison between effectiveness in different fields of health care delivery. In combination with the results of the RCT from the first funding period, this study will allow to estimate the reduction of treatment duration and costs made possible through implementation of treatment manuals derived from the main trial into clinical practice.

Furthermore, this trial has been planned in close collaboration with the parallel trial for short-term cognitive-behavioural therapy (CBT). Endpoints and outcome measures were chosen in accordance with the main trial [7] to allow comparisons between outcomes of the RCT and the transfer studies included in this psychotherapy research network. Outcome measures include internationally used valid and highly relevant measures of SP.

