### Medical Complications

The recording of adverse events will be restricted to psychological conditions. Formally, they are defined as any disorder classified by the International Classification of Diseases F00-F99 ("Mental and Behavioral Disorders").

A serious adverse event (SAE) is an adverse event that may occur at any time of the treatment phase or up to 6 months after end of treatment: results in death; is life-threatening; requires subject hospitalization or prolongation of existing hospitalization; results in persistent or significant disability/incapacity; is a congenital anomaly/birth defect

Changes in mental disorders according to ICD-10 F00-F99 will be specifically asked for in the CRF pages filled by the interviewer at the following time-points: after 25 session of treatment; twelve months after end of treatment.

Any AE (according to the study specific definition) reported by the subject or detected by the local investigator will be collected during the trial and must be documented in the CRF. ICD-10 will be used by the local investigator to code the event. The standard coding system for adverse events, MedDRA, has been reported to be inadequate in psychotherapeutic studies [26]. The clinical course of the AE will be followed until it has changed to a stable condition or until end of follow-up phase, whatever comes first.

In case of SAEs Ethics Committee (EC) and Data Safety Monitoring Board (DMSB) will be informed within 24 hours after the SAE becomes known.

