## Discussion

The study is designed as an extension to the larger multi-site project in which Cognitive-Behavioral Therapy (CBT) and Short Term Psychodynamic Psychotherapy (STPP) of Social Phobia based on SET have been evaluated [7]. It combines the benefits of randomized controlled trials and naturalistic studies. We will ascertain to what degree practitioners integrate the new methods into their clinical routine. Furthermore, the study will determine whether the new methods lead to an improvement of treatment course and outcome and also whether the treatment effects of manualized STPP in routine psychotherapeutic treatment are comparable to those of the controlled, strictly manualized treatments of the main study. This study estimates potential reductions of treatment duration and costs by implementation of treatment manuals into clinical practice.

In contrast to the previous RCT in this study the patients are not recruited by the participating centres. Patients will seek treatment in the regular way of the German health care system attending private practitioners. Therefore, participating therapists recruit patients and announce them to the study centres. In the previous RCT treatments were limited to 25 sessions. In our study therapists are completely free to determine treatment duration. Accordingly, we determined primary outcome after 25 sessions. Our comparison group is naturalistically treated with standard psychodynamic psychotherapy without any additional training of the therapists.

Examinations of these issues in a methodologically rigorous manner will be of high relevance not only for the domain of social phobia but for the dissemination of innovative psychotherapeutic treatments in general.

Implementing the best obtainable treatment into the practice of experienced psychotherapists can be expected to increase treatment effectiveness. While evidence for the efficacy of Supportive Expressive Psychotherapy (SET) and other variants of Short Term Psychodynamic Psychotherapy (STPP) has accumulated [22,23], there has been a lack of studies on the transfer of manualized treatments to routine psychodynamic practice. Our study will be the first one to directly examine the effects of an additional training in a manualized and highly effective STPP procedure on outcome in routine psychotherapy for social phobia.

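### The SAE window runs with treatment length, so if the manual shortens treatment as hypothesised, unadjusted SAE numbers would favour the trained arm at equal event rates

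*Protocol article*

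**What the plan says.** All references are to the Protocol article.

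- **Window.** Safety aspects includes "all serious adverse events that are reported during and up to six months after treatment". Medical Complications repeats this in the SAE definition: an SAE "may occur at any time of the treatment phase or up to 6 months after end of treatment".
- **Treatment length.** The manual has a nominal length (Interventions: "The treatment is designed for a time limited approach with 25 individual sessions of STPP over 6 months"). No length is given for the control arm: "Those patients who are treated in the control condition will receive standard psychodynamic treatment". The Discussion then removes any cap for the trial as a whole: "In our study therapists are completely free to determine treatment duration". The Assessment section provides for longer treatments: "If treatment exceeds 25 sessions additional post-treatment assessment is performed immediately after termination".
- **Expected difference.** The second major hypothesis reads "Implementation of manualized STPP will lead to an average reduction of treatment duration and costs" (Objectives and hypotheses).
- **Analysis.** Secondary analyses says only "Serious adverse events and drop-outs will be analysed descriptively".
- **Diagnoses.** Changes in ICD-10 F00-F99 disorders are actively asked for twice: after session 25, and a year after treatment has ended (Medical Complications).

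**The concern.** The time during which an event can count as an SAE is set after randomisation, by a quantity that the intervention is meant to change. Take an event 14 months after treatment began. In a patient treated for 6 months it lies outside the definition, because the window closed at month 12. In a patient treated for 12 months it is an SAE, because the window runs to month 18.

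For efficacy the authors dealt with free duration: the Discussion gives it as the reason for placing the primary endpoint after 25 sessions. SAEs have no comparable anchor.

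At stake is how the safety table is read. If the arms are observed for different lengths of time and the table does not show it, equal risks can look like an advantage for the manual, and a moderate excess of harm can look like parity.

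**Working it through.** The protocol states no figure for exposure or SAE frequency, so there is none to reproduce. The check is arithmetic on the windows.

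**Inputs**
- SAE window per patient: T + 6 months, where T is treatment duration (Safety aspects, Medical Complications).
- Span covered by the active enquiry about diagnoses: up to T + 12 months (Medical Complications).
- Trained arm: T = 6 months, the nominal length under Interventions. This is a simplification, because trained therapists are also free to go on.
- Control arm: T is not stated. Assumed means are 6, 9, 12 and 18 months.
- Constant event hazard, equal in both arms (assumption).

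**Formulas**
- Expected control/trained SAE ratio = (T_control + 6) / (T_trained + 6).
- Expected control/trained ratio for new diagnoses over the whole span = (T_control + 12) / (T_trained + 12).

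| Assumed mean control duration (months) | SAE windows, control/trained | SAE ratio | Diagnosis spans, control/trained | Diagnosis ratio |
|---|---|---|---|---|
| 6 | 12/12 | 1.00 | 18/18 | 1.00 |
| 9 | 15/12 | 1.25 | 21/18 | 1.17 |
| 12 | 18/12 | 1.50 | 24/18 | 1.33 |
| 18 | 24/12 | 2.00 | 30/18 | 1.67 |

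**Reversal.** If trained-arm treatments averaged 9 months and control treatments 6, the SAE ratio would be 12/15 = 0.80, against the manual.

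**Masking.** At a mean control duration of 12 months, a monthly rate 1.5 times higher in the trained arm gives 1.5 × 12 = 18 units of expected events. The control arm gives 1 × 18 = 18. The raw numbers would look equal.

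**In events.** With 105 patients split evenly (52.5 per arm), a control mean of 12 months and an assumed 0.05 SAEs per patient-year, the trained arm expects 52.5 × 0.05 × 12/12 = 2.6 and the control arm 52.5 × 0.05 × 18/12 = 3.9. At an assumed 0.10 per patient-year the figures are 5.3 and 7.9.

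**After the change.** With events per patient-month, or a window of the same length from start of treatment in both arms, the expected ratio at equal constant hazards is 1.00 whatever the control duration.

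**The case against.** The strongest reply is that the protocol never says raw counts will be compared. It says the analysis is descriptive, and events per patient-month are descriptive too. The denominator is a detail that an analysis plan may supply, and an unequal window distorts nothing once exposure is accounted for. This stands in part: a reader might infer that the protocol commits to unadjusted counts, and it does not. But the SAE definition itself is fixed here and ends at T + 6. A common-window table from start of treatment cannot be complete under that definition for anyone who stops before month 6, whatever a later plan says.

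A reader might also infer that the safety table favours manualized STPP by construction. The documents do not support that. Duration is free in both arms, the extra assessment for long treatments is not confined to controls, and the imbalance arises only if mean durations really differ as hypothesised.

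Nor do the SAE ratios carry over to new diagnoses. The first enquiry is tied to session 25, the same anchor as the primary endpoint, and the second gives a span of T + 12, so the distortion is smaller.

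Finally, the consequence is limited. Adverse events are restricted to mental and behavioural disorders, no safety test or safety hypothesis is planned, and at the lower assumed rate the difference is about one event (3.9 − 2.6 = 1.3). Each SAE also goes to the ethics committee and the safety board within 24 hours, so oversight during the trial does not depend on the final table. All of this stands and limits the weight of the point. It does not make an unadjusted comparison between arms sound.

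**Conclusion.** The point holds conditionally. The protocol ties SAE observation time to treatment duration, leaves duration free, and hypothesises that it is shorter in the trained arm. If that hypothesis is true, raw SAE numbers would favour manualized STPP at equal event rates, and nothing stated in the protocol corrects for it.

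The direction follows from the text and the second hypothesis. The size does not: the SAE ratios of 1.00 to 2.0 and the diagnosis ratios of 1.00 to 1.67 rest on assumed control durations, a trained arm held at 6 months, and a constant hazard. The point concerns how a secondary, descriptive safety comparison will be read. It does not touch the primary endpoint.

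**What to change.** 1. State that SAEs are reported by arm as events per patient-month observed, with total observed time per arm beside them.
2. Add a table of SAEs within a common window from start of treatment. Twelve months is one example: the nominal 6 months of treatment plus the 6 months already stated. This comparison does not rely on a constant hazard, whereas the rate does.
3. Word the SAE definition so that an event inside the common window counts even if it falls more than 6 months after an early end of treatment. For a patient who stops at month 2, the present window closes at month 8.
4. Report new F00-F99 diagnoses found at the 25-session enquiry separately from those found at the later one.

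No new visits or patients are needed. Follow-up to 12 months after termination reaches at least month 12 from start for everyone who stays in it, and adverse events are already collected throughout the trial. The rates need dates for start and end of treatment and for last observation. The article does not list these, but treatment duration cannot be compared under the second hypothesis without the first two. The cost is a slight rewording of the SAE definition and one extra table. The small downside is that late events in long treatments leave the common-window table and appear only in the rate table.
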